**FIGURE 4 F4:**
[figure not shown]
Schematic architecture and workflow of the ProVIA-Kids app.

The app’s primary function is to fill out questionnaires, evaluate them automatically, and provide further assistance to users. These functions are grouped together in the Questionnaire Module (see Figure 4–4, 13, 14a, 15b, 15c). For example, users can fill out a profile questionnaire for themselves or the children in their care (see Figure 4-4). Configurable rules (see Figure 4–15c) calculate value spaces from the given answers, which in turn can be assigned to different recommendation texts (see Figure 4–5) and displayed to the user (see Figure 4–6). For example, for a question about the number of hours of sleep, the answer given can be assigned to one of the two recommendation texts “insufficient sleep” or “correct amount of sleep” (also depending on age, for example). The user can also access further information independently of the displayed recommendations via the knowledge section containing articles on different topics (see Figure 4–7). In addition to profile questionnaires, the app also offers a questionnaire for behavioural analysis of a situation with a child in care (see Figure 4–8). For this questionnaire, recommendations can also be calculated and displayed to the user (see Figure 4–9, 10), and further articles can be offered (see Figure 4–11). Already completed questionnaires and their recommendations can be recalled in a list-based history view (see Figure 4–12). The app also offers visual feedback on all behavioural analyses grouped according to the answers given (see Figure 4–13). For example, it can be quickly identified if a particular behaviour only occurs at a specific time of day, during certain activities, or only with specific users.

Knowledge Base articles (see Figure 4–14a) offered in the app (see Figure 4–7, 11) are stored in an external database formatted as Markdown documents (see Figure 4–14b) and can be delivered to the app via a web interface (see Figure 4-14c). Therefore, a developed Markdown parser maps the articles and their contents (e.g., text or images) during display (see Figure 4–7, 4–11).

App questionnaires are defined in Excel files and can thus be quickly customised by non-technical personnel (see Figure 4-15a). These Excel files are stored in a GitHub repository, are converted to JSON configuration files by a GitHub Action when modified, and are added to a new build of the app (see Figure 4–15b). Recommendations are generated based on JSON configuration files (see Figure 4–15c). These include a mapping from answer value spaces (“conditions”) to Markdown documents. For example, a recommendation for a child’s mood in behaviour analysis is displayed if the following condition is evaluated to “true” by a developed expression parser: answer[“child-mood”]===“good” && answer[“child-mood-good”]!==“relaxed.”

The app also lets the user enter their daily mood in a mood diary (see Figure 4-17) and display it in a 7- or 30-days view (see Figure 4-16). In addition, the app can display a daily reminder to fill out the mood diary as an app push notification with the user’s consent (see Figure 4-18).

Questionnaires completed by the user (i.e., profile questionnaires, behavioural analysis questionnaires, and mood diary questionnaires) are stored locally as answersheets in encrypted storage (see Figure 4-19a). Completed questionnaires are pseudonymized (see Figure 4–19b, 19c), then sent transport-encrypted to a REST API service (see Figure 4-19d) (Pryss et al., 2018; Vogel et al., 2021) and stored in a relational database (see Figure 4–19e). The API service and the database are hosted in the UKW data center. Researchers of the participating research institutes can evaluate the stored questionnaires with the help of analysis software (see Figure 4–20) and generate reports (see Figure 4–21).

The app follows a model-driven approach: the individual pages or modules are implemented as web components in TypeScript and Sass or CSS, while the control flow logic, questionnaires, recommendations, and associated knowledge base articles can be variably adapted to the needs of the study to be conducted using various JSON-based configuration files. Hence, questionnaires and recommendations are dynamically generated and displayed based on users’ answers.

### Primary and secondary outcomes

#### Primary outcome

The “Eltern-Belastungs-Inventar” [EBI (Tröster, 2011), the German version of the Parenting Stress Index] measures various facets of parental stress with 48 items. In addition to the EBI total scale, the questionnaire contains five subscales that capture distress sources located in the child (distractibility/hyperactivity of the child, acceptability, demandingness, adaptability, and mood), and seven subscales to capture impairment in parental functioning (attachment, isolation, competence, depression, health, role restriction, spouse/parenting partner relationship). The questionnaire shows an excellent internal consistency for the total scale (Cronbach’s Alpha, α = 0.95), the child subscale (α = 0.91) and the parent subscale (α = 0.93. The EBI shows good test-retest-reliability for the total scale (*r* = 0.87) and the subscales (child subscale: *r* = 0.85 and parent subscale: *r* = 0.87) (Irlbauer-Müller et al., 2017).

#### Secondary outcomes (exploratory)

●The intensity of the child’s challenging behaviour (aggression toward others, aggression toward objects, auto-aggression, screaming, refusal, cursing) is assessed on a 5-point scale (0 = not applicable, 5 = very pronounced). The frequency of CB in those four categories is also recorded.●Caregiver mood, stress level, self-care and app use are recorded daily via an ecological momentary assessment on a 5-point scale in the app. Means for each week are calculated.●The “Fragebogen zum Kompetenzgefühl von Eltern” (FKE (Miller, 2001), German Version of the Parenting Sense of Competence Scale) uses 16 items to measure two aspects of parents’ self-esteem: satisfaction with the parenting role (frustration, feelings of failure, motivation) and sense of self-efficacy (competence, problem-solving skills, success). The internal consistency for the English version is acceptable (α = 0.76) and the test-retest-correlations range between *r* = 0.46–0.82 (Gibaud-Wallston and Wandersman, 1978; Johnston and Mash, 1989).●The short form of the “Erziehungsfragebogen” (EFB-K (Naumann et al., 2010), German version of the Parenting Scale) captures the parental reaction to challenging behaviour with 13 items. Of particular interest is contingency management, which is supposed to be influenced by the app. The internal consistency is acceptable (α = 0.76) (Miller, 2001).

#### Additional parent variables for sample description

●The short form of the “Resilienz-Fragebogen” [RS13 (Leppert et al., 2008)] measures caregivers’ coping ability. The two factors Personal Competence and Acceptance of Self and Life are captured by 13 items. The internal consistency is excellent (α = 0.90) and the test-retest-reliability is good (*r* = 0.61)●The German version of the “Emotion Regulation Questionnaire” [ERQ (Abler and Kessler, 2009)] measures self-reported preference for the emotion regulation strategies *reappraisal* and *suppression*. The questionnaire contains ten items on dealing with positive and negative emotions. The internal consistency ranges between α = 0.68 and 0.82.●The “Fragebogen zur Erfassung von Ressourcen und Selbstmanagementfähigkeiten” [FERUS (Jack, 2007)] comprises seven scales (motivation for change, self-observation, active and passive coping, self-efficacy, self-verbalisation, hope, social support). It measures health-related resources and self-management skills with 66 items. The questionnaire has a good to excellent internal consistency (α = 0.86–0.93) and a good test-retest-reliability (*r* = 0.66–0.86) (Znoj and Baumgartner, 2008).●For the assessment of psychiatric symptoms in caregivers, the Symptom Checklist-90-R [SCL-90-R (Derogatis, 1977)] was used. The questionnaire contains 90 items and describes in 9 scales the domains somatization, obsessive-compulsive disorder, interpersonal sensitivity, depression, anxiety, hostility, phobic anxiety, paranoid ideation, and psychoticism. The questionnaire has excellent internal consistency (α = 0.96–0.98) and a very good test-retest-reliability (*r* = 0.79–0.90, for the interval of 1 week) (Franke, 2002).

#### Additional child variables for sample description

●The “Verhaltensfragebogen bei Entwicklungsstörungen” (VFE (Steinhausen and Winkler Metzke, 2005), German version of the “Developmental Behaviour Checklist” [Einfeld and Tonge, 1995)] measures a wide range of challenging behaviour and emotions in children with developmental disabilities with 96 items. The questionnaire contains five scales (disruptive/antisocial, self-absorbed, communication disturbance, anxiety, social-relating). The questionnaire shows good internal consistency for four scales (α = 0.69–0.90) with the exception of the anxiety subscale (α = 0.58). The test-retest-reliability is high (between *r* = 0.83 and *r* = 0.89, for the interval of 1.8 years).●The Sensory Profile 2 [SP 2, (Dunn, 2017)] measures sensory processing with 38 items. The questionnaire shows good internal consistency (between α = 0.72 and α = 0.91).●The “Fragebogen zur Sozialen Kommunikation” [FSK, (Bölte and Poustka, 2005)] assesses abnormal social interaction and communication patterns and stereotypical behaviour with 40 items. The internal consistency of the total scale (α = 0.83) and the test-retest-reliability (*r* = 0.76, for intervals between 6 months and 2 years) are good.

#### Control variables

●As control variables, participants’ treatment motivation, treatment expectancy, and readiness to change are assessed using the “Fragebogen zur Erfassung der Veraenderungsbereitschaft” (FEVER (Hasler et al., 2003), German Version of the University of Rhode Island Change Assessment Scale). FEVER captures the temporal-motivational dimension of the change process with 24 items. The questionnaire shows good internal consistency for the scales (between α = 0.72 and α = 0.86).

#### Evaluation of the app

To evaluate the quality of the psychoeducational content, user will be asked to provide feedback for each intervention module on the comprehensibility and scope of the information and frequency of use of the recommendations. The app’s technical aspects are evaluated using the Mobile Application Rating Scale: user version (uMARS). The uMARS shows an excellent internal consistency (α = 0.90) (Stoyanov et al., 2016). The participants are also asked to provide information about points of criticism and suggestions for improvement regarding the content of the app and the app in general in an open format.

For an overview of all measures used throughout the study, please refer to Table 2.

**TABLE 2 T2:** Instruments and measurements.

		Baseline T0	Post intervention T1	Follow-up T2
**Caregiver variables**				
Sociodemographic questionnaire	Sociodemographic data			
EBI	Caregiver stress	X	X	X
RS13	Resilience	X		
ERQ	Emotion regulation	X		
FERUS	Ressources and self-management	X		
FKE	Parental Competence	X	X	X
EFB-K	Parenting scale	X	X	X
SCL-90-R	Psychiatric symptoms	X		
Mood	Daily scores (assessed via app)	during intervention		
Caregiver burden	Daily scores (assessed via app)	during intervention		
**Child variables**				
Base data	Prior treatments, IQ, CGI			
Challenging behaviour	Frequency/severity of challenging behaviour	X	X	X
VFE	Challenging behaviour	X		
SP2	Sensory Processing	X		
FSK	Social communication (ASS)	X		
ADOS	ASS symptoms (observation)			
ADI	ASS symptoms (parent interview)			
**Evaluation of treatment**				
FEVER	Readiness for change	X		
Treatment expectation		X		
Treatment motivation		X		
Adverse events			X	X
Treatment satisfaction			X	
uMARS			X	
**User data**				
Evaluation of intervention modules				

#### Sample size and power calculations

The calculation of the sample size (software: G*Power Version 3.1) is based on the primary outcome “Change in total score of EBI from T0 (baseline) to T1 (after treatment; 8 weeks)” using a two-sided *t*-test with a power of 80% at a significance level of 5%. The expected effect size is based on the following considerations: A parent training programme for parents of children with intellectual developmental disorder and challenging behaviour showed an effect size of *d* = 0.63 (η = 0.09) for the reduction of parental stress experience (Hudson et al., 2003). Apps as stand-alone procedures for the treatment of depressive symptoms (comparable to resource building components in ProVIA) meta-analytically show an effect size of *d* = 0.33 (Weisel et al., 2019). Based on the assumption that app-based interventions generally produce effects of lower strength, but that ProVIA contains resource-building interventions for caregivers in addition to parent training components, we assume an effect size of *d* = 0.6. We will need *N* = 19 participants to detect an effect of this size and aim at a sample size of *N* = 25 to compensate for dropouts.

### Statistical analyses

All statistical analyses will be performed with IBM SPSS Statistics Version 26. The primary analysis is based on an intention-to-treat approach, i.e., participants will be analysed, irrespective of whether they discontinued the treatment or other protocol violations are revealed. Participants are included if treatment was started. Changes in the primary outcome (EBI score from T0 to T1 and T0 to T2) will be evaluated with paired-samples *t*-tests. For additional exploratory analyses, possibly relevant covariates are assessed in a repeated measures analysis of covariance. Changes in secondary outcomes are examined using paired *t*-tests. The relationship between parental resilience (RS13), emotion regulation (ERQ) and resources and self-management skills (FERUS) and the degree of change in parental stress experience (difference in EBI total scale from T0 to T1) is tested using correlation analyses in an exploratory manner. Intention-to-treat refers solely to the treatment, i.e., the use of the ProVIA-Kids app. We will analyse data from all participants from which we have T0 and T1 or T0 and T2, respectively. Study drop-outs with whole missing assessments will be excluded from analysis. Missings in individual questionnaires will be handled according to the respective manual. We will tolerate max. 10% missing items. Ten percentage of missing items in total and 1 missing item per scale. If there are no specific instructions, we will use the mean of the respective scale to replace an individual missing value. We expect a very low degree of missingness and drop-outs. However, we will compare complete drop-outs (no T1 or T2 assessment) to the completer group in terms of initial parental stress, initial child problem behaviour, sociodemographic variables (employment, single parenthood, support), and diagnosis to get an idea about factors leading to drop-outs.

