**Methods:**

In this uncontrolled open trial we will enrol *N* = 25 caregivers of children aged 3–11 years with a diagnosis of IDD and/or ASD. Participants will use the ProVIA-Kids app for 8 weeks. During the intervention phase, participants will conduct behaviour analyses after each instance of CB. The app will summarise the identified putative causes for the CB in each situation, and provide recommendations regarding the handling and prevention of CB. Furthermore, the app will aggregate data from all available behaviour analyses and identify the most relevant (i.e., most frequently reported) risk factors. Measurement points are at baseline (T0), after the intervention (T1) and 12 weeks after the end of the intervention (follow-up; T2). The primary outcome is the absolute change in parental stress (EBI total scale) between T0 and T1. Further aspects of interest are changes in CB severity and frequency, caregiver mood, satisfaction with the parenting role (EFB-K total scale) and experienced parenting competence (FKE total scale). Pre-post comparisons will be analysed with paired sample *t*-tests.

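### The Statistical analyses section puts both EBI changes (T0–T1 and T0–T2) under the primary outcome, while the abstract and the sample size section define only T0–T1

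*Protocol article*

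**What the plan says.** Three places in the protocol article attach time points to the primary outcome, and they do not agree.

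- Abstract, Methods: "The primary outcome is the absolute change in parental stress (EBI total scale) between T0 and T1".
- Sample size and power calculations: the outcome on which the trial is sized is "Change in total score of EBI from T0 (baseline) to T1 (after treatment; 8 weeks"), with a two-sided 5% level and 80% power.
- Statistical analyses: "Changes in the primary outcome (EBI score from T0 to T1 and T0 to T2) will be evaluated", in both cases by a paired t-test.

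T2 is the follow-up visit, "12 weeks after the end of the intervention (follow-up; T2"). The Statistical analyses section also sets up a separate data set for each comparison: "We will analyse data from all participants from which we have T0 and T1 or T0 and T2, respectively". The exploratory secondary outcomes are listed under their own heading, and the EBI change from T0 to T2 is not among them. The Statistical analyses section labels its covariate and correlation analyses exploratory, but gives the T0–T2 test no such label.

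**The concern.** A trial with one primary outcome should say the same thing about it wherever it is defined. Here the section that governs the analysis names two changes under the primary label, while the abstract and the power calculation name one. An analysis plan could follow either version and claim to agree with the article.

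At stake is which result decides the trial. If T0–T1 alone decides, the error rate of a positive primary result is the 5% that the sample size section states. If either change may count, there are two chances at that level, and the power calculation describes only one of them. The Discussion states an aim of investigating efficacy, and the Outlook makes transfer of the principle to other disorders depend on promising efficacy results. It therefore matters that a reader can tell which test is meant.

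**Working it through.** **1. The article's own sample size figure.** Inputs from Sample size and power calculations: d = 0.6, 80% power, "using a two-sided *t*-test", 5% level, N = 19 needed, N = 25 planned. Paired t-test power comes from the noncentral t distribution with n − 1 degrees of freedom and noncentrality d√n.

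- Two-sided 5%: n = 24 (power 0.804); power is 0.696 at n = 19 and 0.821 at n = 25.
- One-sided 5%: n = 19 (power 0.808).

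The stated 19 is reproduced only by a one-sided test. That is a separate matter and does not bear on this point. What matters here is that the calculation covers one test, T0–T1.

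**2. Two unadjusted tests, bounds.** With two two-sided 5% tests and no true change, the chance of at least one significant result is at most 0.05 + 0.05 = 10%. If the tests were independent it would be 1 − 0.95² = 9.75%. Counting only results in the beneficial direction, independence gives 1 − 0.975² = 4.94%, against 2.5% for one test.

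**3. Correlation of the two changes.** Both changes subtract the same baseline, so they are correlated. With equal variances, correlation r between T0 and each later visit, and correlation s between T1 and T2 (in units of the common variance):

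- covariance of the two changes = 1 − 2r + s
- variance of each change = 2(1 − r)
- correlation of the changes = (1 − 2r + s) / [2(1 − r)]

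If s = r, this is (1 − r) / [2(1 − r)] = 0.5 whatever r is. Varying a common visit-to-visit correlation therefore tells us nothing about sensitivity; the change-score correlation itself has to be varied. If T1 and T2 are closer to each other than to baseline (s > r), it exceeds 0.5 and the inflation shrinks.

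**4. Simulation.** The documents do not give the change-score correlation, so a range is assumed. Each setting used 400,000 replicates with normal data, no true change and the same caregivers in both comparisons.

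| Assumed correlation of changes | Either test significant, n = 25 | Same, n = 19 | Beneficial direction only, n = 25 |
|---|---|---|---|
| 0.3 | 9.4% | 9.5% | 4.7% |
| 0.5 | 9.1% | 9.2% | 4.6% |
| 0.7 | 8.4% | 8.5% | 4.2% |
| 0.9 | 7.0% | 7.1% | 3.5% |

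The single-test level (5% two-sided, 2.5% in the beneficial direction) is exceeded at every value tried.

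**5. If both changes were meant as primary.** A Bonferroni split (two-sided 2.5% each) needs 29 evaluable caregivers for 80% power at d = 0.6. Power per comparison is 0.726 at n = 25 and 0.576 at n = 19. The planned 25 does not reach 80% for two primary tests under that split.

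**The case against.** The strongest reply is that the article often uses the term primary outcome for the measure and not for a contrast. The section The ProVIA trial names parental stress as the primary clinical outcome, and the section headed Primary outcome describes the EBI without any time point. On that usage, the Statistical analyses sentence says only that the EBI is tested at both later visits, with the deciding contrast fixed in the abstract and the sample size section. The same section also uses the T0–T1 difference for its correlation analyses, and Table 2 labels T2 as follow-up. This reading is tenable, so it cannot be taken as settled that the article intends two primary tests.

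A reader might go further and infer three things that the documents do not support.

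- That success at either visit counts as a positive primary result. No section says so. The error rates above are conditional on that rule, and on applying to both tests the 5% level that the article states only for T0–T1.
- That the time point is free to be chosen after the data are seen. The published abstract and power calculation already name T0–T1, which limits that freedom.
- That the absence of a testing order or a split of the 5% is itself a fault. Such detail is commonly left to an analysis plan, which is not shown.

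The inconsistent label survives all of this. The Statistical analyses section is the only place that gives the T0–T2 change any status, and the status it gives is primary.

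It is also fair that little hangs on a few points of error here. Study design and trial flow describes a pre-post trial without a control group, aimed at usability and suitability and to be followed by a randomised trial. Neither p-value can attribute a change in stress to the app.

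**Conclusion.** The point holds as an inconsistency in the current text about which comparison is primary. It does not show that the trial will claim success at either visit. If it did so at the two-sided 5% level, the family-wise error would be about 7% to 9.5% for assumed change-score correlations of 0.9 to 0.3, or about 3.5% to 4.7% against 2.5% in the beneficial direction. That is a moderate inflation and less than a doubling. It rests on the either-visit rule, normal data, the same caregivers at both visits and a correlation that the documents do not give. The correction is worth making because it settles which test decides the trial, but the uncontrolled design and the planned randomised trial limit the consequence.

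**What to change.** Reword the sentence in Statistical analyses along these lines: *The single primary analysis is the change in EBI total from T0 to T1, by a paired t-test at the two-sided 5% level. The change in EBI total from T0 to T2 is a secondary follow-up analysis and cannot on its own support a positive primary result.* For consistency, add the T0–T2 change to the list of secondary outcomes.

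This agrees with the abstract and the sample size section. It needs no split of the 5%, costs no power for T0–T1 and requires no further participants. The cost is that a significant result at T2 alone can no longer be called a primary success.

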### General challenges related to mental health applications

Beyond the technical and content-related aspects, there are some fundamental challenges with regard to the medium of MHAs, which will be briefly discussed here. In their recent review, Bauer and colleagues discuss various risks associated with MHA (Bauer et al., 2020). There seems to be a group of people who do not use health applications (HA) for various reasons or do not find them attractive (Krebs and Duncan, 2015) due to e.g., a general lack of interest, (hidden) costs or data protection concerns. ProVIA-Kids addresses the data protection risks through pseudonymisation and the storage of data on a secure server at the University Hospital of Würzburg. The project’s public funding and the resulting independence from private-sector interests or advertising partners contributes to a high standard of data protection and ensures that the app remains completely free of charge. However, even among people who are open to using HAs, the use of the HAs or interventions to be carried out independently (including online programmes) in general shows highly variable and often low retention rates, especially outside the study context. Since motivation and commitment are essential, ProVIA-Kids was designed to be attractive for users, e.g., by addressing them personally and using interactive elements such as a mood diary.

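### The primary analysis is labelled intention-to-treat for everyone who started the app, but it uses only available T0–T1 pairs and has no analysis for a missed T1 visit

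*Protocol article*

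**What the plan says.** All the rules stand in one paragraph of the protocol article, Statistical analyses. It opens with the label: "The primary analysis is based on an intention-to-treat approach, i.e., participants will be analysed, irrespective of whether they discontinued the treatment". It adds that having started treatment is enough to be included. Later it limits the label to use of the app and defines the data used: "We will analyse data from all participants from which we have T0 and T1 or T0 and T2, respectively". It then states "Study drop-outs with whole missing assessments will be excluded from analysis".

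The test is a paired-samples t-test. Replacement by the scale mean covers single missing items only, and nothing is stated for a whole missed visit. The justification is "We expect a very low degree of missingness and drop-outs". Caregivers with no T1 or T2 assessment are to be compared with completers on initial stress, child behaviour, sociodemographic variables and diagnosis.

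Two other places matter. The abstract fixes the target: "The primary outcome is the absolute change in parental stress (EBI total scale) between T0 and T1". Study design and trial flow says that caregivers who discontinue the intervention are encouraged to attend the remaining assessments.

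**The concern.** The two inclusion rules cannot both define the primary set. A caregiver who began using the app and has no T1 score belongs to the first set and not to the second.

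The choice affects the estimate. The trial has one arm, so the mean T0–T1 change among those analysed is the whole result, and no control group exists in which similar loss might offset the bias. If caregivers without T1 benefited less, the mean over available pairs overstates the change in all who started. If those with the highest T0 stress are lost, regression to the mean makes the remaining pairs understate it. The baseline comparison of drop-outs may show that loss was selective, but it leaves the estimate unchanged, and with at most a handful of drop-outs it has little power to show even that.

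**Working it through.** **Inputs from the article.** 19 needed and 25 enrolled to allow for drop-outs, d = 0.6, two-sided 5%, power 80% (Sample size and power calculations). EBI total test-retest r = 0.87 (Primary outcome). No drop-out rate is given anywhere.

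**The plan's own figure.** I used the exact noncentral t for a paired test, with df = n − 1 and noncentrality 0.6·√n. The stated two-sided test needs 24 pairs (power 80.4%). With 19 pairs, power is 69.6%. The figure of 19 is reproduced only by a one-sided 5% test (80.8%). That is a separate matter, but it bears on this one: the margin 6/25 = 24% is only what 19 and 25 imply. It is used below as the upper end of an assumed range of 4%, 12% and 24%.

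**Case A: loss related to benefit (assumed).** Those with T1 improve by 0.60 SD of change and those without T1 by 0. The mean over all starters is 0.60 × (1 − loss), and the overstatement is 1/(1 − loss) − 1.

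| Loss | All starters | Available pairs | Overstatement |
|---|---|---|---|
| 4% | 0.576 | 0.60 | 4% |
| 12% | 0.528 | 0.60 | 14% |
| 24% | 0.456 | 0.60 | 32% |

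I simulated this case at 24% loss unrelated to T0, with r = 0.87, n = 25 and 6,000 runs. The paired estimate averages 0.60. The likelihood estimate from T0 and T1 also averages 0.60. Setting missing T1 to T0 gives 0.45 to 0.46. The mixed model therefore does not remove this bias, and the no-change analysis does.

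**Case B: loss related to T0 stress (assumed).** The log-odds of loss rise by 1.5 per SD of T0, T1 = r·T0 − 0.30 + error, and units are SD of the EBI score. The bias in the mean change over available pairs is −(1 − r) × E[T0 | T1 observed]. Numerical integration gives E[T0 | T1 observed] = −0.267, −0.143 and −0.053 at 24%, 12% and 4% loss.

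| Loss | r = 0.5 | r = 0.7 | r = 0.87 |
|---|---|---|---|
| 24% | 0.13 | 0.08 | 0.035 |
| 12% | 0.07 | 0.04 | 0.02 |
| 4% | 0.03 | 0.02 | 0.007 |

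For example, at 24% and r = 0.87: 0.13 × 0.267 = 0.035, so the mean over available pairs is −0.265 against a true −0.30. Simulation agrees. At 24% the paired means lie near −0.165, −0.22 and −0.265 for the three correlations (0.5, 0.7, 0.87), so the bias at r = 0.5 is 0.13 to 0.14. The likelihood estimate stays within about 0.003 of −0.30 throughout. The direction here understates benefit. It would reverse if the least stressed caregivers were lost.

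**No selective loss.** If missing T1 is unrelated to baseline and to benefit, the paired estimate is unbiased and only precision is lost.

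**The case against.** The case for the plan has real strength. The article states openly that its intention-to-treat label refers only to app use. A caregiver who stops using the app but completes T1 stays in, and such caregivers are encouraged to attend. Stopping the app and missing T1 are therefore different events, and the analysis is not a treatment-completer analysis. This stands: the label misleads rather than conceals.

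A reader might infer three stronger points that the article does not support.

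- **That the expectation of few drop-outs is contradicted by the section on general challenges of mental health applications.** That section reports "highly variable and often low retention rates, especially outside the study context", but it concerns use of health apps and self-directed interventions. It does not concern attendance at study assessments, and non-users who attend remain in the analysis.
- **That the plan foresees 24% drop-out.** It states no rate. A recruitment margin does not contradict an expectation of low loss, and the 19 behind it does not match the stated test.
- **That testing T0–T1 and T0–T2 on different sets is itself a flaw of the primary analysis.** Statistical analyses does list both comparisons under the primary outcome, but the abstract and the sample size section define it as T0–T1 only. Using available pairs for a separate follow-up comparison is ordinary.

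It is also fair to say that Case B is small at the only correlation the article gives, and that a mixed model does nothing for Case A. A trial aimed at usability ahead of a randomised trial may not need a refined estimator, although the Discussion also states an efficacy aim. These points limit the size of the concern. They do not remove the conflict between the two inclusion sentences or supply an analysis for a missed T1.

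**Conclusion.** The point holds in a limited form. The article includes all who started treatment and then analyses only those with both T0 and T1, so the primary analysis is an available-pairs (assessment-completer) analysis under an intention-to-treat label. Because the exclusion rule is stated, this is a stated choice and not a detail left to a fuller document.

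The bias is conditional on why T1 is missing. With no change in those lost, the overstatement is 4% to 32% over 4% to 24% loss. With loss driven by T0 stress, the bias runs from under 0.01 SD (4% loss, r = 0.87) to about 0.14 SD (24% loss, r = 0.5). Loss rates, the log-odds of 1.5 and the correlations of 0.5 and 0.7 are assumptions. The value 0.87 is the reported test-retest figure, and the correlation across an 8-week intervention could be lower. If loss proves very low or unrelated to stress and benefit, the effect on the result is negligible. The change is worth making because it is cheap and needs no new data.

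**What to change.** 1. Reconcile the two inclusion sentences, and call the paired t-test set available pairs.
2. Take the primary estimate as the T1–T0 contrast from a linear mixed model for EBI total at T0, T1 and T2 (time as factor, unstructured covariance, REML) in all caregivers who started the app. This uses the T0 score of those without T1, and their T2 score where they have one.
3. Keep the paired t-test as a supportive analysis.
4. Add a sensitivity analysis that sets missing T1 to the caregiver's T0 score. State that the mixed model corrects only loss explained by observed scores and that this analysis covers lack of benefit in those lost. Read it for the mean, since fixing changes at exactly zero also shrinks their spread.

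The cost is a few sentences and two further runs. The downside is a slightly more complex model in a sample of 25. With complete data the contrast equals the paired mean difference, so the estimate loses nothing if drop-out is as low as expected.
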